### Power analysis

Based on our six EBQI/F intervention sites and six control sites, Table 3 presents detectable slopes (*i.e*., within-phase performance change) and changes in slopes (between phases) assuming first: low, medium and high values for the residual standard deviation (σ), the variances of the random intercepts (*v*_*a*_) and slopes (*v*_*b*_), and a first order auto correlation, ρ, among the observations within a site; then, power of at least 0.8 on a two-sided test made at the 0.05 significance level. Using ASSIST study findings, we estimated residual standard deviations (σ) ranged from 8.9% to 11.9%, *v*_*a*_ from 53.4 to 167, *v*_*b*_ from 4.4 to 6.6, and within-site first order auto correlations (ρ) from 0.10 to 0.53. We used the minimum, midrange, and maximum of the estimates to respectively present best case (σ = 8.9%, *v*_*a*_ = 53.4, *v*_*b*_ = 4.4, ρ = 0.10), expected (σ = 10.1%, *v*_*a*_ = 137.6, *v*_*b*_ = 5.3, ρ = 0.26), and worst case (σ = 11.9%, *v*_*a*_ = 167.0, *v*_*b*_ = 6.6, ρ = 0.53), scenarios. Given the low rates of metabolic monitoring and management observed in preliminary studies, the detectable changes would be both possible and clinically meaningful.

**Table 3 T3:** Detectable differences in slope (% change per month)

**Hypotheses**	**Best case scenario**	**Expected scenario**	**Worst case scenario**
**Implementation has no effect over phase**	3.7%	4.3%	5.1%
**Implementation is no different from control at each phase**	5.3%	6.1%	7.2%

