### Existing VA practice, patterns and outcomes

Both VA [7,20-22] and non-VA [23-25] studies have found low rates of metabolic monitoring among patients treated with antipsychotics. Surprisingly, there are no published studies that examine the rates for management of metabolic side-effects that develop in the context of newly-initiated antipsychotic treatment or antipsychotic medication changes, although substantial improvement is likely needed in these practices as well. In a recent study of 32 VA facilities, metabolic monitoring frequency was greater at baseline (*i.e*., within 30 days before to 30 days after the new prescription date) than at initial follow-up (*i.e*., 60 to 120 days after prescription date), although at both times monitoring was low. For example, baseline monitoring rates compared to follow-up rates were 67% versus 49% for weight, 46% versus 27% for glucose or hemoglobin A1c, and 32% versus 16% for LDL [20].

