The protocol presented in this article is for the project, ‘Monitoring and Management for Metabolic Side Effects of Antipsychotics,’ which is testing an EBQI/F implementation intervention to enhance uptake of evidence-based tools and strategies to improve monitoring and management of metabolic side effects of antipsychotics concurrently with the MIAMI Project’s VA national implementation effort. We anticipate that the national implementation effort will improve care overall, although the improvement is likely to be variable as there are a substantial number of facilities that have fewer resources and more difficulty mounting QI efforts, and that do not have formal coordination between mental health and primary care clinics for managing metabolic side effects in patients taking antipsychotics. Therefore, we are studying the national implementation effort at multiple sites, using a cluster randomized design, assessing organizational challenges at these sites, and testing an intervention that includes EBQI [29,30] and external facilitation [31,32] strategies to customize, adapt and enhance the impact of local strategies for implementation of the national QI initiative. We stratified sites based on scores on an organizational practice survey, and randomized at the site level, recognizing that organizational context is likely to be a strong predictor of implementation success. Results will inform ongoing VA implementation of tools and strategies to improve metabolic monitoring and management, as well as future implementation research to improve care at all VA facilities, not just sites that have adequate resources and QI infrastructure.

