#### Metabolic side-effect monitoring

Data will be extracted for all patients who were treated at a study site and were prescribed a new antipsychotic medication (defined as a ‘new antipsychotic start’ or the addition of, or switch to, an antipsychotic medication that had not been prescribed in the previous 180 days) [20] and who would be due for monitoring or management of metabolic side effects during any of the three six-month phases of the study. If monitoring of a metabolic parameter (weight, glucose or hemoglobin A1c, and low-density lipoprotein [LDL]) is documented as occurring within the window of 30 days before to 30 days after a new prescription, we defined this as completed ‘baseline’ monitoring. The recommended 90-day ‘follow-up’ monitoring is defined as monitoring of a metabolic parameter between 31 and 120 days following the new prescription date. For each study site, the proportion of patients due for monitoring that received monitoring at each time point for each parameter will be calculated and aggregated for each month in each study phase. All patients whose monitoring window ends within a given month will be included in the denominator to calculate that month’s (baseline or follow-up) monitoring rate.

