### Data analysis

Because weight gain is a common antipsychotic side effect that increases risk of diabetes and cardiovascular disease [6,9,11], and overweight/obesity is prevalent in patients with psychotic disorders [10,11], the primary outcome measures for the proposed project will be the extent to which weight/BMI is monitored and to which overweight or obese patients receive a guideline-concordant weight management intervention. At each site, the proportion of patients who receive baseline monitoring, follow-up monitoring, and management of metabolic abnormalities will be measured each month against those who were due for such actions during the same time period. We expect EBQI/F intervention sites to gradually increase performance on monitoring and management measures over time. Therefore, we will conduct a time series analysis of monthly performance, with each site contributing six monthly performance measures in each of the three phases of the study. These analyses will estimate the change in rates of baseline monitoring during the Implementation Phase due to intervention (national quality improvement initiative with and without EBQI/F), and allow comparison of these performance changes between sites receiving EBQI/F and those not. Further, these analyses will allow within-phase changes in monitoring rates to be compared between phases; *e.g*., for EBQI/F sites, is the monitoring performance change during the Implementation Phase different from that during the Sustainability Phase? We will similarly collect, summarize, and analyze data from all patients due for follow-up metabolic monitoring and metabolic management (as defined in Table 1) during the three study phases.

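### The expected power inputs are not the midranges they are said to be, and the claim that the detectable changes are possible is unsupported for the between-arm comparison of baseline weight monitoring

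*Protocol article*

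**What the plan says.** The Power analysis section of the protocol article takes ranges for four variance parameters from a previous study (ASSIST): residual SD σ 8.9 to 11.9, random-intercept variance v_a 53.4 to 167, random-slope variance v_b 4.4 to 6.6, and autocorrelation ρ 0.10 to 0.53. It says how the scenarios were formed: "We used the minimum, midrange, and maximum of the estimates to respectively present best case", followed by the expected and worst cases. The expected values listed are σ 10.1, v_a 137.6, v_b 5.3 and ρ 0.26.

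The calculation is "Based on our six EBQI/F intervention sites and six control sites", with "power of at least 0.8 on a two-sided test made at the 0.05 significance level". Table 3 gives detectable slopes (best / expected / worst) of 3.7 / 4.3 / 5.1 for change within a group and 5.3 / 6.1 / 7.2 for intervention against control, in percent per month. The section ends by pointing to low preliminary rates of monitoring and management and concluding that "the detectable changes would be both possible and clinically meaningful".

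The Data analysis section makes weight/BMI monitoring and weight management the primary outcomes, "with each site contributing six monthly performance measures in each of the three phases of the study". For current practice, the section on existing VA practice reports, from a study of 32 VA facilities, that "baseline monitoring rates compared to follow-up rates were 67% versus 49% for weight".

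**The concern.** The concern has two parts.

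- **Label.** A midrange is (minimum + maximum) / 2, and the expected inputs do not look like that. If they are some other statistic, the text misdescribes how the central power scenario was built.
- **Ceiling.** A slope of 6.1 points per month sounds modest until it is carried through a six-month phase. A measure that starts at 67% has only 33 points left. If the slope the trial can detect needs that much or more, the trial lacks 0.8 power for any attainable effect on that measure, and the feasibility sentence hides this.

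A non-significant between-arm result on baseline weight monitoring could then be read as evidence against the intervention, when the design could detect only a rise to nearly complete monitoring.

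**Working it through.** **1. Reproduce Table 3.** Inputs: 6 sites per arm, 6 monthly points per phase, two-sided α 0.05, power 0.8, and the listed σ, v_b and ρ. With a separate intercept per site, v_a does not enter the slope variance.

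- Variance of one site's slope: V = v_b + the variance of a generalised least-squares slope over 6 monthly points with AR(1) residuals (σ, ρ).
- Standard errors: √(V/6) within a group and √(2V/6) between groups.
- Detectable slope = standard error × the multiplier for 80% power from a noncentral t. The article gives no degrees of freedom; 15 is assumed here, giving a multiplier of 2.998.

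| Scenario | V | Within group | Stated | Between groups | Stated |
|---|---|---|---|---|---|
| Best | 4.4 + 4.96 = 9.36 | 3.74 | 3.7 | 5.30 | 5.3 |
| Expected | 5.3 + 7.16 = 12.46 | 4.32 | 4.3 | 6.11 | 6.1 |
| Worst | 6.6 + 10.57 = 17.17 | 5.07 | 5.1 | 7.17 | 7.2 |

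All six entries match after rounding. Ordinary least squares with 18 df gives 3.70/4.29/5.10 and 5.24/6.07/7.22, within about 1.2% of the table, so the result does not hinge on the assumed df.

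**2. Midranges of the quoted ranges.**

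| Parameter | (min + max) / 2 | Listed as expected |
|---|---|---|
| σ | (8.9 + 11.9)/2 = 10.4 | 10.1 |
| v_a | (53.4 + 167)/2 = 110.2 | 137.6 |
| v_b | (4.4 + 6.6)/2 = 5.5 | 5.3 |
| ρ | (0.10 + 0.53)/2 = 0.315 | 0.26 |

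None agrees. The three that drive slope variance (σ, v_b, ρ) are all listed on the favourable side. With true midranges, V = 5.5 + 7.80 = 13.30, and the detectable slopes become 4.46 and 6.31, about 3% higher. Power at the stated 4.3 and 6.1 is then about 0.77.

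**3. End-of-phase position.** Six monthly measures span five intervals; a full six months is six. The between-arm slope implies these differences:

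- Best: 5 × 5.3 = 26.5 to 6 × 5.3 = 31.8 points
- Expected: 5 × 6.1 = 30.5 to 6 × 6.1 = 36.6 points
- Worst: 5 × 7.2 = 36.0 to 6 × 7.2 = 43.2 points

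Added to starting rates with flat controls:

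| Measure (quoted start) | Best | Expected | Worst |
|---|---|---|---|
| Baseline weight (67%) | 93.5-98.8% | 97.5-103.6% | 103.0-110.2% |
| Follow-up weight (49%) | 75.5-80.8% | 79.5-85.6% | 85.0-92.2% |
| Baseline glucose or HbA1c (46%) | 72.5-77.8% | 76.5-82.6% | 82.0-89.2% |
| Baseline LDL (32%) | 58.5-63.8% | 62.5-68.6% | 68.0-75.2% |

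From 67%, the largest constant slope that stays within 100% is 33/6 = 5.5 to 33/5 = 6.6 points per month. The within-group slopes from 67% end at 85.5-89.2%, 88.5-92.8% and 92.5-97.6%, below 100% throughout.

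**4. Windows behind the starting rates.** The quoted 67% uses 30 days either side of the prescription, the same baseline window as the trial. The quoted 49% uses days 60 to 120, while the trial counts "monitoring of a metabolic parameter between 31 and 120 days following the new prescription date". The trial's window contains the narrower one, so the rate in the same patients cannot be lower. The size of the increase cannot be derived from the article.

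**The case against.** The strongest reply is that the table is right and that the feasibility sentence speaks of monitoring and management in general.

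- **Table 3 is not miscalculated.** This stands. A reader might infer from the midrange mismatch that the power calculation fails, but the entries reproduce and the correction is about 3%. The section also calls its inputs low, medium and high, so another central statistic may have been meant; then only the label is wrong.
- **Most cells have room.** This also stands. The within-group row, the best-case between-arm slope, follow-up weight at the quoted 49%, glucose and LDL all stay below 100%. Weight management, the other primary outcome, has no starting rate on the trial's definition. A reader might infer that the detectable changes are impossible across the board, or that 0.8 power is never available for baseline weight monitoring. The figures do not support either: over five intervals even the expected case ends at 97.5%.
- **The 67% is borrowed.** It comes from 32 facilities in another study, and the trial sites' rates are not given. Lower site rates would leave more headroom. However, sites were selected on low weight-programme use and on survey scores, not on low weight monitoring, so the article gives no reason to expect much lower rates.
- **Flat controls.** The article says "We anticipate that the national implementation effort will improve care overall", which would raise the end rate that intervention sites need. It also says that few providers use the national resources and expects a flat pre-implementation trend. Flat controls are a fair working assumption; a falling control slope would ease the ceiling.

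A reader might also conclude that the trial cannot detect a realistic gain. The article gives no figure for a realistic gain, so that is not shown.

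**Conclusion.** The concern holds in a limited form.

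1. The expected inputs are misdescribed. True midranges raise the expected detectable slopes from 4.3 and 6.1 to about 4.5 and 6.3 points per month. This is a small correction that does not alter the design.
2. The unqualified feasibility claim is not supported for the between-arm comparison of baseline weight monitoring. Here 0.8 power requires near-universal monitoring within one phase in the best case, is at or over the ceiling in the expected case, and cannot be reached in the worst case.

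The second conclusion matters more, because it concerns part of a primary outcome in the comparison that answers the trial's effectiveness question. It rests on three assumptions: a 67% starting rate at the trial sites, flat controls, and a constant slope over five to six monthly intervals. The first depends on the analysis model and df assumed above, which reproduce the published table.

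**What to change.** - State which statistic the expected inputs are, or recompute the expected column with true midranges (about 4.5 and 6.3).
- Add to Table 3 the implied end-of-phase between-arm difference: about 27-32, 31-37 and 36-43 points in the best, expected and worst scenarios.
- Limit the feasibility sentence to measures with enough headroom. For each primary measure give the starting rate used and its source, saying that 67% and 49% come from other facilities and that the 49% uses a narrower follow-up window than the trial's. Preferably use the sites' own pre-implementation rates on the trial's definitions, since retrospective data are already being collected.
- For baseline weight monitoring, say scenario by scenario where 0.8 power stands against the ceiling; do not say that it is unavailable in every scenario.

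The cost is rewording and a short recalculation. No new sites or data are needed. The stated figures become slightly less favourable.

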### Trial status

The study is in the initial part of the Implementation Phase. The initial EBQI site visits to the six implementation sites were completed in 2012, and facilitation activities have begun at the intervention sites. Retrospective data are now being collected from all study sites.

## Discussion

This study will build on prior research, demonstrating the effectiveness of EBQI and facilitation to support tailored implementation efforts at a site, and addresses an important aspect of clinical care for patients taking antipsychotics. Improving monitoring for metabolic side effects of antipsychotics, as well as promoting timely evidence-based management when these effects emerge, will lead to improved patient safety and long-term outcomes. This project aims to increase uptake of the existing tools and strategies that have been made available through a national dissemination effort, although the facilitation process could result in refinements of these elements or in development of new improvement approaches. We discuss strengths and initial challenges of the study below.

### Site selection

The research team employed a systematic site selection process rather than identifying a convenience sample of frequently-utilized study sites. The selected sites thus are more likely to be representative of the diversity of VA facilities, with respect to size, extent of academic affiliation, resources available to pursue quality improvement efforts, and scores on the organizational practice survey than would have been the case if a convenience sample of sites was selected. Systematic site selection ensures that study findings will be broadly generalizable to the majority of VA facilities, and enables the research team to identify unique site implementation barriers and facilitators.

Despite the potential benefits of this site selection method, it also has caused challenges. While we pursued IRB approval, our contacts at 3 of the 12 initially selected sites indicated that the site would be unable to participate in the study (*e.g*., because the leader who originally agreed was no longer in the same position). This experience suggests that a disadvantage of the systematic site selection process is that there may be more attrition than when convenience sampling is employed; perhaps investigators could develop retention strategies to maintain site leaders’ interest in the study and encourage them to overcome participation barriers during the sometimes lengthy waiting period between grant submission and final funding. A study team could include back-up sites in the site selection approach, although it may not be possible to activate a replacement site once the study has started. Finally, investigators should recognize that a site that withdraws after the start of implementation activities should still be included in an ‘intent-to-implement’ analysis.

### Timing of EBQI/F intervention

The grant application was written in 2008, with the expectation that the EBQI/F intervention could be initiated concurrently with the planned initiation of the MIAMI Project dissemination and implementation activities. The national training for the MIAMI Project occurred in 2010. However, due to the time elapsed between grant submission and IRB approval, and a subsequent delay related to obtaining data access and approval for use of our automated computer routines, the study intervention site visits did not begin until late 2011, more than a year following the start of MIAMI Project activities. Therefore, the project is studying the added effect of EBQI/F on top of an ongoing dissemination effort, rather than a test of the effectiveness of EBQI/F delivered at the time that a national implementation activity was rolled out, as was originally envisioned. This means that during the ‘Pre-implementation Phase,’ both intervention and control sites have MIAMI Project resources available, rather than this period representing a baseline period prior to MIAMI Project roll-out. However, relatively few providers avail themselves of the educational information, computer routines, or support services. Thus, we expect that the EBQI/F intervention could result in substantial improvement in monitoring and management practices.

### Definition of abnormal ranges for glucose and LDL

Evidence- and consensus-based guidelines recommend obtaining plasma glucose and lipid tests in the fasting state, and intervening if test results are elevated (*e.g*., glucose ≥126 mg/dL; LDL ≥130 mg/dL) [17,18]. Unfortunately, neither VA databases nor the narrative electronic medical record reliably indicate whether a patient was fasting at the time of laboratory testing [20]. Therefore, our study uses higher cut-off points (glucose ≥200 mg/dL; LDL ≥160 mg/dL) in order to increase the likelihood that elevated glucose or LDL are, in fact, indicative of diabetes or dyslipidemia respectively and warrant management action(s), rather than being an artifact of the non-fasting state. Other methods could be used to determine whether the patient was likely to be fasting, such as the length of time between the clinical visit and the tests; the administration of glucose and lipid assays on the same day, which could indicate that the tests were intended to be drawn in the fasting state [49]; or examining chart documentation for evidence that fasting was recommended prior to testing. However, this information may be incomplete and may vary among providers and sites. In contrast, using the higher cut-offs for Objective 2 analyses will increase the likelihood that abnormal glucose or LDL tests are truly abnormal and require some form of management. This method reduces false positives and increases specificity at the cost of reduced sensitivity.

We also chose to focus our Objective 2 examination of management actions on those patients whose testing indicated obesity (BMI ≥30) or weight gain (>5%), rather than including the larger group of patients who warrant management for being overweight (BMI between 25 and 30). It would not be feasible to review the medical records for all patients with BMI greater than or equal to 25. Excluding these patients, as well as patients with possible abnormal glucose or LDL values, represents a limitation in the study methods. We will further explore this issue by conducting a sensitivity analysis by assessing the extent to which side-effect management takes place for a subsample of patients who are overweight, have blood glucose between 126 and 200 mg/dL, or have LDL between 130 and 160 mg/dL. We will also explore whether chart documentation indicates that a given blood test was meant to be obtained while the patient was fasting. These sensitivity analyses could provide useful information for future studies and could be used to encourage inclusion of fasting notations in the VA databases.

Despite the challenges and limitations of this complex study of implementation strategies, this ongoing study will yield insights into barriers and facilitators to monitoring and management of antipsychotic side effects; determine the effectiveness of EBQI combined with external facilitation with regard to promoting successful implementation; and hopefully will improve care and patient safety at the intervention sites. Study findings will inform subsequent VA efforts to improve care and safety for patients prescribed antipsychotic medications.

## Abbreviations

ASSIST: A study of strategies for improving schizophrenia treatment; ADA: American diabetes association; APA: American psychiatric association; BMI: Body mass index; CATIE: Clinical antipsychotic trials of intervention effectiveness; CPG: Clinical practice guidelines; DoD: Department of defense; EQUIP: Enhancing quality and utilization in psychosis; EBQI/F: Evidence-based quality improvement with facilitation; FPG: Fasting plasma glucose; FE: Formative evaluation; LDL: Low-density lipoprotein; MH QUERI: Mental health quality enhancement research initiative; MIRECC: Mental illness research, education, and clinical center; MIAMI: MIRECC initiative on antipsychotic monitoring improvement; OIG: Office of inspector general; OL: Opinion leader; PARIHS: Promoting action on research implementation in health services; SGA: Second-generation antipsychotic; SMI: Serious mental illness; SMM: Survey on metabolic side-effect monitoring and management; VistA: Veterans health information systems and technology architecture; VISN: Veterans integrated service network.
